## Abstract

**Background:**

The use of analgesics can lead to cases of drug abuse and dependence. It can also cause pseudo-addiction in patients suffering from pain. What is the actual situation in patients suffering from severe sickle-cell disease, exposed to acute pain during vaso-occlusive crises? Evaluation of the use of analgesics, on the basis of Diagnostic and Statistical Manual of Mental Disorders criteria for substance abuse and dependence, makes it possible to differentiate the symptoms occurring only in a context of pain, in the aim of managing the pain, and thus describing pseudo-addiction, from symptoms also occurring when there is no pain, and more in favour of true addiction. Currently there is no data available in France on this problem, and no studies have been carried out in children or adolescents with sickle-cell disease. The purpose of the study is to evaluate the prevalence of problematic use of equimolar mixture of oxygen and nitrous oxide and other analgesic drugs in a population of subjects with severe sickle-cell disease in France.

**Methods/design:**

PHEDRE (Pharmacodépendance Et DREpanocytose-drug dependence and sickle-cell disease) is an observational, descriptive and transversal study. Patients under the age of 26 with sickle-cell disease are included in the study by the doctors looking after them in sickle-cell disease centres. The patients are then contacted by a trained researcher for a telephone interview, including an evaluation of the Diagnostic and Statistical Manual of Mental Disorders criteria for abuse and dependence to equimolar mixture of oxygen and nitrous oxide and for each of the analgesic drugs taken by the patient. The data are also completed using the subject’s medical record.

**Discussion:**

This study will make it possible to provide an initial quantitative and qualitative evaluation of problematic use of equimolar mixture of oxygen and nitrous oxide and analgesic drugs in the sickle-cell disease population. The results will be used firstly to provide additional data essential for monitoring the risk of overdose, abuse, dependence and misuse of these products, and to begin awareness-raising and to provide information for health care professionals, in order to significantly improve the management of sickle-cell disease-related pain.

**Trial registration:**

Clinical Trials.gov ID: NCT02580565 registered 16 October 2015

Unique Protocol ID: RC14_0344

## Background

Equimolar Mixture of Oxygen and Nitrous Oxide (EMONO) is a gas mixture that contains equal parts of each. It has Marketing Authorization (MA) in France since 2001. It is especially indicated in short-term analgesia for painful procedures or in the event of mild to moderate pain in adults and children over the age of one month.

Dependence on and tolerance to the effects of nitrous oxide have been demonstrated in animals and in humans [1–4]. Numerous cases of nitrous oxide abuse having led to adverse effects have been reported in literature [5–18]. Variability in the effects experienced with nitrous oxide is described in numerous studies [19], ranging from dysphoria to euphoria. Concerning EMONO, there is little literature on the potential of abuse, as few countries have the mixture as a drug. In the United States, the gas is delivered by pharmaceutical companies to professionals, who then perform titration themselves. Cases of severe abuse and dependence to EMONO have however been declared to the French addiction monitoring system via the network of Centres for the Evaluation of and Information on drug Dependence (Centres d’Evaluation et d’Information sur la Pharmacodépendance - CEIP-A). Analysis of these cases showed that it concerned patients in a serious medical situation, requiring repeated use of EMONO in hospital, and that a certain number of these subjects suffered from severe Sickle-Cell Disease (SCD). It therefore appeared that the SCD population could represent a high risk population for EMONO abuse or dependence. Thus, a specific data collection in these subjects was needed.

Sickle-cell anaemia and severe SCD are haemoglobinopathies from the group of corpuscular hereditary haemolytic anaemias. In France, patients with SCD are managed via a patient-oriented care network, especially Reference Centres or Special Centres for Children and Adults (RSCCA). These centres are scientific and clinical excellence structures for rare diseases such as SCD. The RSCCA medical practitioners see each patient, regardless of their age, at an inpatient/or outpatient consultation, at least once per year as part of routine follow-up. The acute pain caused by Vaso-Occlusive Crises (VOC) are the most common clinical symptom and the first cause that lead to the emergency department for children, adolescents and adults with SCD. Patients are also prone to chronic or recurrent acute pain, that require analgesics taken at the patient’s home. This pain is subject to significant inter-individual variability but also intra-individual variability, as much in terms of severity, site and duration of the pain episode [20, 21]. The unforeseeable nature of the pain and extent of the active pain relief strategies (called coping strategies), developed by patients with SCD, are different from other painful disorders in which similar analgesic treatment is used, and imply the difficulties patients and health care professionals experience in managing it [21, 22]. According to the intensity of the pain and type of treatment and according to the World Health Organisation’s (WHO) classification, level I analgesics, (acetaminophen and Non-Steroidal Anti-Inflammatory drugs (NSAIDs)), level II (codeine, tramadol, nalbuphine) and level III (morphine) can be used. EMONO is ideal for the rapid management of pain and/or in combination with morphine in hospital in children and adolescents [21, 23]. One of the barriers to management of pain in patients with SCD is the reticence of health care professionals to use morphine-based analgesics, for fear of the patient developing drug dependence [21]. Indeed, the request for analgesics can be perceived, not as a response to the pain episode but as a drug addiction [24, 25], whereas most often it is a simple clinical impression [26]. Nevertheless, undertreated pain exposes patients to the risk of “pseudo-addiction”, which occurs when patients attempt to obtain a stronger analgesic dose, thus possibly coming across resistance from the nursing team. These behaviours, which look like the compulsive search for analgesic drugs, are interpreted as being addictive-like-behaviour and widely keep the beliefs of the healthcare team as to the dependence of their patients. However in pseudo-addiction, analgesic-seeking behaviour stops when the pain is treated effectively and does not persist after pain relief has been achieved [27]. Evaluation of the use of analgesic drugs, on the basis of Diagnostic and Statistical Manual of Mental Disorders (DSM) criteria for substance abuse and dependence [28], makes it possible to differentiate the symptoms occurring only in a context of pain, in the aim of managing the pain, and thus describing pseudo-addiction (common), from symptoms also occurring when there is no/mild pain, and more in favour of true addiction (rarer). The major risk is that these patients who, in order to deal with their pain, demonstrate behaviour compatible with substance use disorder criteria, receive fewer analgesics and in whom therefore treatment is not optimal [29–31]. Also, if genuine drug addiction to analgesics was identified, it would require treatment adjustment. A specific evaluation is therefore necessary in order to improve patients’ management. The role of EMONO and opiate analgesics in the treatment strategy, the potential for abuse and dependence to which is well known, today require special monitoring of the risk of overconsumption, abuse and dependence in this population.

Currently there are no data available in France on this concern, and no studies have been carried out in children or adolescents with SCD. This lack of data is all the more significant when we know that childhood experiences and those in adolescence can determine emotions and behaviours and strategies for adaptation to events in adulthood. The main objective of this study is to evaluate the prevalence of problematic use of EMONO in a population of subjects with severe SCD treated in RSCCA in France. The secondary objectives are:To evaluate the prevalence of problematic use of other WHO level II and III analgesic drugs used in the treatment of pain in patients with SCD treated in RSCCA in France.To describe and to characterize problematic use of EMONO and other analgesic drugs.To study the relationships between the existence of problematic use of analgesic drugs (EMONO and/or other analgesics) and the other study evaluation parameters (sociodemographic, clinical and therapeutic data and consumption of other psychoactive substances).

## Methods/Design

### Study design

It is an observational, descriptive, transversal study aiming to determine the prevalence of problematic use of EMONO and other analgesic drugs in subjects with SCD treated in RSCCA. Subjects with SCD are recruited by medical practitioners of RSCCA. Thereafter, data are collected by a scheduled telephone interview and with subject’s medical record.

This project received the financial backing from the French National Agency for Medicines and Health Products Safety (Agence Nationale de Sécurité du Médicament et des produits de santé – ANSM) as part of the 2014 ‘Young Scientist’ request for proposals.

### Setting of the study

The CEIP-A in Nantes, is the coordinating investigation centre in charge of the general management, monitoring and coordination of the project. A consortium was set up with the partner CEIP-A in charge of coordinating the project at local level in their research area (CEIP-A in Clermont-Ferrand, Lille, Marseille, Paris and Toulouse). The RSCCA participating in the study are spread over metropolitan France territory. The RSCCA medical practitioners are in contact with the CEIP-A in Nantes and with the CEIP-A in their area. The period of inclusion for each participating medical practitioner is 12 months and the period of data collection is 15 months. There is no follow up after the patient’s assessment.

For this national multicentric study, a multi-disciplinary steering committee, comprising pharmacologists from the participating CEIP-A, medical practitioners working in RSCCA, a methodologist biostatistician, a clinical research staff and a psychiatrist specialising in addiction was set up in order to draft the study protocol. Its missions are to ensure the study is valid in terms of scientific content and methodology. The steering committee should handle any practical problems occurring during the study and where appropriate, decide on amendments to the protocol. It shall meet on a regular basis and whenever necessary, to approve aspects concerning practical organisation and to answer any questions raised during the study.

### Participants

#### Eligibility criteria

The patients are recruited for the study by their doctor when they come to the RSCCA for their routine treatment or follow-up, according to the following inclusion criteria:Subject with confirmed SCD diagnosis, regardless whether it is the homozygous or heterozygous formSubject treated for SCD at a RSCCA participating in the study, regardless of the duration of the illnessSubject under the age of 26Written consent from adult subjects and written consent from one of the parents or legal guardians of minors (under 18)

The study exclusion criteria are the following:State-protected adult (under guardianship)Subject not having the general aptitude to participate in the study assessment (i.e. not able to respond to the telephone interview): too young, insufficient motor development, major difficulties understanding the French language and/or speech and/or hearing disorders.

### Patient recruitment

Each medical practitioner in the RSCCA participating in the study recruits SCD patients over a 12-month period. If the patient meets all inclusion criteria, the medical practitioner asks him, and his parents or legal guardian if the subject is a minor, if he wishes to participate in the study, and provides clear and appropriate verbal information on the study (objectives, scientific interest, and practical procedures).After a cooling-off period, he collects the patient’s written consent (and from at least one of the parents or the legal guardian for minors).

To facilitate schedule of the telephone interview and the collection of study data during the telephone interview, the patient has to complete two additional forms:The “inclusion form” is completed directly with the medical practitioner during the outpatient/inpatient consultation. This form contains identification of the RSCCA, name of the medical practitioner, name of the patient, phone number, birthdate, moment when patient can be called (days, hours). The inclusion form and written consent will be sent at the same time by secure messaging to the Nantes CEIP-A by the medical practitioner.The “analgesic list form” is completed by the patient alone or/and with his family (for minors) after the medical consultation but before the telephone interview. The patient should complete the form with all analgesic drugs he has taken (at home and in hospital) over the last 12 months (names and frequencies).Then, the medical practitioner has to complete a short clinical assessment.

The inclusion form and written consent are triplicate documents. One copy is given to the patient, one is sent by the medical practitioner to the Nantes CEIP-A, and one is kept in the RSCCA. The clinical assessment completed by the medical practitioner is also kept in the RSCCA. Once included in the study, patients will undergo a single assessment by phone, without subsequent follow-up.

### Consent for participation

At inclusion, the patients receive an information leaflet for their age range (as do the parents of minors). Then, they sign a consent form. For minors, parents also sign a consent form authorizing their children’s participation.

### Ethics statement

This non-interventional study received authorisation from the French data protection body (Commission Nationale de l’Informatique et des Libertés – CNIL) and a favourable opinion from the French advisory board for data processing in health care (Comité Consultatif sur le Traitement de l’Informatique en matière de Recherche dans le domaine de la Santé – CCTIRS) and from the local ethics committee (Groupe Nantais d’Ethique dans le Domaine de la Santé – GNEDS).

### Variables and data measurement

Data for the analysis are collected in two steps: through the clinical assessment completed by the medical practitioner and through a single telephone interview.

### Clinical assessment

After he includes a patient, the medical practitioner completes a clinical assessment which contains all information about patient’s family and personal history, history of the SCD and treatment already received for SCD. Every six months, the trained researcher will schedule a visit to the RSCCA to retrieve the clinical assessments of all patients included in this RSCCA and enter the data in the electronic case report form (e-CRF).

### Telephone interview

When Nantes CEIP-A receipts the inclusion form and written consent, the trained researcher schedules a telephone interview with the patient. Telephone interview is carried out with a trained researcher from Nantes CEIP-A. The interview is suited to the child’s, adolescent’s or young adult’s age, maturity and comprehension skills. During the telephone interview, data are stored in the electronic case report form (e-CRF). The following parameters are evaluated during the telephone semi-structured interview for EMONO, and for other analgesic drugs, during pain episodes and outside pain episodes:*Prevalence of problematic use*:

Problematic use is abuse of or dependence on a substance according to the fourth edition of DSM (DSM-IV), and substance use disorder according to the fifth edition (DSM 5). At the time the protocol was written, we used DSM-IV criteria because the DSM 5 was not yet translated in French. The DSM-IV identifies seven substance dependence diagnostic criteria and four substance abuse diagnostic criteria. Abuse is defined by at least one of the four DSM-IV criteria of substance abuse and drug dependence by at least three of the seven DSM-IV criteria of substance dependence.2.*Description and characterisation of problematic use:*

Consumption will be evaluated on the basis of quantitative and qualitative responses on the effects sought, quantitative and qualitative responses to each substance abuse and dependence criterion, by separating the pain-related criteria and non-pain-related criteria and quantitative and qualitative responses on craving.3.*Study of the relationships between problematic use and the other study evaluation parameters*

The outcome measures are sociodemographic, clinical and therapeutic data and data on consumption of other psychoactive substances, and their relationship with problematic use of analgesic drugs. This study will be used to demonstrate any factors relating to problematic use of analgesic drugs, or even a specific analgesic drug.

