### Statistical methods

All evaluation parameters will be subjected to a descriptive analysis. The quantitative variable evaluation parameters will be described using position parameters (mean or median) and dispersion (standard deviation, interquartile range, range). Normality of their distribution will be assessed (normality test and evaluation using the relevant graphic tools). The qualitative variable evaluation parameters will be shown in the form of number and frequency tables for each modality. The primary outcome measure will be evaluated by the frequency of subjects with EMONO problematic use compared to the overall study population. The secondary outcome measures will be assessed by the frequency of subjects demonstrating problematic use of one or several other analgesic drugs, compared to the overall study population, by estimating the occurrences of positive responses for the various effects sought when taking analgesic drugs, for each DSM-IV substance abuse and dependence criterion, for each pain-related criterion, and non pain-related criterion (if the DSM-IV substance abuse and dependence criteria are met), and for craving. The frequencies will be estimated for EMONO and for each of the other analgesic drugs, the use of which is identified as problematic. The relationships between problematic use of analgesic drugs (EMONO and/or others) and the other study evaluation parameters will be assessed by univariate analysis and the appropriate statistics tests, depending on the type of variable and the size of the study population (parametric or non-parametric tests). The existence or absence of problematic use can then be studied as a dependent variable in a multivariate analysis (i.e. logistic regression) in order to test the relationship with independent variables selected from the previous analysis. No intermediate analysis or subgroup analysis is to be carried out in this study*.*

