The Nantes CEIP-A is competent in the assessment of drug dependence and has recognised expertise in this field. It has conducted several studies evaluating consumption of psychoactive substances. This positive experience confirms the feasibility of these assessment methods for the Nantes CEIP-A and will therefore ensure the collection of quality data in the PHEDRE project.

The use of DSM-IV criteria could be seen as a limitation since the DSM 5 [32] is now translated and therefore usable in French. But we initially choose to assess both DSM-IV dependence and abuse criteria in addition with craving and finally, this set of criteria is consistent with the DSM 5 substance use disorders diagnostic criteria.

PHEDRE is the first study which proposes to evaluate problematic use of EMONO and analgesics in the French SDC population. We believe that differentiating pseudo-addiction from real substance use disorder will enable clinicians to adapt patient management: increase analgesia in pseudo-addiction, provide an addictological follow-up for the others.

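### The primary EMONO prevalence has no condition on pain context, and the planned per-criterion split does not show how many subjects have pseudo-addiction or addiction

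*Protocol article*

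**What the plan says.** **Case definition** (Telephone interview). Problematic use is DSM-IV abuse or dependence. The abuse threshold reads "Abuse is defined by at least one of the four DSM-IV criteria of substance abuse". For dependence, three positive answers out of seven are required. Neither threshold mentions pain.

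**Primary analysis** (Statistical methods). "The primary outcome measure will be evaluated by the frequency of subjects with EMONO problematic use compared to the overall study population". This is one figure.

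**Where the pain split appears** (Statistical methods). The secondary outcomes count positive responses "for each pain-related criterion, and non pain-related criterion (if the DSM-IV substance abuse and dependence criteria are met), and for craving". The unit is the criterion, and the split is conditional on meeting DSM-IV. The regression uses presence or absence of problematic use as its dependent variable, without a pain condition.

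**Rationale.** Background says that the DSM evaluation "makes it possible to differentiate the symptoms occurring only in a context of pain, in the aim of managing the pain, and thus describing pseudo-addiction". It sets these against symptoms that persist with little or no pain, which it takes as a sign of true addiction and expects to be the less frequent pattern. Discussion adds: "We believe that differentiating pseudo-addiction from real substance use disorder will enable clinicians to adapt patient management".

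**Data collection** (Telephone interview). The sentence that introduces the list of interview parameters says they are assessed both during and outside pain episodes. The first parameter in the list is the prevalence of problematic use.

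**The concern.** The distinction that motivates the study is between kinds of subject: those whose symptoms occur only in pain, and those whose symptoms also occur without it. The planned outputs are one pooled count of subjects and a table of criteria. Neither says how many subjects belong to each kind.

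A subject whose criteria occur only in pain counts towards the headline prevalence exactly like one whose criteria also occur outside pain. Background calls the first pattern common and the second rarer, and warns that pain-driven behaviour is mistaken for dependence. A single percentage labelled abuse or dependence invites the same mistake, and the regression would relate risk factors to a mixed outcome.

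**Working it through.** The protocol states no prevalence, power or sample-size figure that could be reproduced. The check therefore asks whether the planned outputs determine the number of subjects in each group.

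**Step 1: the pooled frequency alone.** Let P be the pooled prevalence and s the unknown share of DSM-positive subjects who would count as addiction. Addiction prevalence is P × s and pseudo-addiction prevalence is P × (1 − s), ignoring mixed cases for the moment. Inputs: N = 2000, the article's estimate of potentially eligible patients (Study size), which is not a target; P = 10%, assumed.

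- The 95% half-width is 1.96 × √(0.10 × 0.90 / 2000) = 1.3 percentage points. With P = 5% it is 1.0 point, and with P = 20% it is 1.8 points.
- With s = 0, addiction is 0% and pseudo-addiction 10%. With s = 0.5 they are 5% and 5%. With s = 1 they are 10% and 0%.

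The pooled figure could be estimated quite precisely and still fit every split.

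**Step 2: adding the per-criterion frequencies.** Suppose each criterion is positive outside pain in a share p of problematic users (p assumed). Assume too that the pain-context answers place no further restriction, for example because they are frequent enough to make every subject DSM-positive.

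For at least 3 of 7 dependence criteria, the mean number of positive criteria per subject is 7p.
- The largest possible share places exactly three positives on as many subjects as possible: 7p / 3.
- The smallest gives some subjects all seven and the rest two: max(0, (7p − 2) / 5).

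| p | smallest share | largest share |
|---|---|---|
| 10% | 0% | 0.7 / 3 = 23% |
| 20% | 0% | 1.4 / 3 = 47% |
| 30% | 0.1 / 5 = 2% | 2.1 / 3 = 70% |
| 40% | 0.8 / 5 = 16% | 2.8 / 3 = 93% |

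For at least 1 of 4 abuse criteria, the share lies between p (the same subjects each time) and min(1, 4p) (different subjects each time). At p = 10% that is 10% to 40%.

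A linear-programming search over all response patterns gave the same limits. Marginal criterion frequencies therefore do not fix the number of subjects who meet the rule outside pain.

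**Step 3: subjects who fit neither description.** Take a subject with no abuse criterion, two dependence criteria only in pain and one outside pain. If criteria from both contexts are added, three of seven is reached. Outside pain alone, the rule is not met. Yet the symptoms are not confined to pain, so Background's description of pseudo-addiction does not fit either. Two classes are not enough.

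**Step 4: the boundary.** The Abstract contrasts pain with no pain, Background with no or mild pain, and Telephone interview with time outside pain episodes. A criterion present during mild pain could be classified differently under each.

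**The case against.** The strongest reply has four parts.

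1. **The primary outcome matches the primary objective.** The objective is the prevalence of problematic use, and that is what is defined and counted. Characterising it is a secondary objective, and the split by criterion serves that. This stands: nothing requires the pooled figure to lose its primary place.

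2. **The data are there.** Pain context is collected for each subject and drug, so a subject-level split can be derived. This also stands. A reader might infer that the study cannot give a prevalence of pseudo-addiction or addiction. The documents do not support that; they show only that the listed analyses do not include one.

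3. **Two prevalences may have been meant.** The sentence introducing the interview parameters allows that reading. But Statistical methods then plans one frequency, so the ambiguity is itself something to resolve. Likewise, a reader might take it as a stated rule that criteria from the two contexts are added together. The text neither says so nor excludes it.

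4. **This is a condensed article.** A derivation rule may sit in the full protocol or analysis plan. That is fair, so the absence of an algorithm is not the point. The point is what the article does fix: one pooled primary frequency and a split by criterion.

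A reader might also infer from Background's common and rarer that the headline overstates addiction several-fold. If 75% to 90% of positive subjects were positive only in pain, a reported 10% would leave 2.5% to 1% with criteria outside pain. Those inputs are assumptions. The documents give no proportion, and the primary outcome is labelled problematic use, not addiction. The figures should not be presented as the size of an error.

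**Conclusion.** The point holds in limited form. As listed, the analyses yield one pooled EMONO prevalence and marginal criterion frequencies, and these do not determine how many subjects show pseudo-addiction or addiction, although the article gives that distinction as its rationale. The 2% to 70% range at p = 30% shows how little the marginals settle. It rests on an assumed p and on unrestrictive pain-context answers, and it does not estimate bias in this study. The pooled prevalence remains a valid answer to the primary objective as worded. This is an inexpensive improvement to make before analysis, not a flaw that invalidates the primary outcome.

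**What to change.** Keep the pooled prevalence as the primary figure, and state whether criteria from the two contexts are added to reach the thresholds and whether a prevalence per context is also intended. Beside it, for each drug, assign every DSM-positive subject to one class:

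- **(a)** the DSM-IV rule is met counting only criteria present outside pain;
- **(b)** mixed: the rule is met only when pain-context criteria are added, but at least one criterion is also present outside pain;
- **(c)** all positive criteria occur only in pain, which is the pseudo-addiction pattern described in Background.

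If the pooled rule counts a criterion present in either context, the classes are exclusive and sum to the pooled figure. Report each as a share of the study population with a 95% CI. Use one definition of the boundary between pain and no pain throughout. Add class (a) as a further outcome in the association analysis if there are enough events.

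The cost is some wording and one derived variable per drug; the context data are already planned. The drawback is fewer events per class, hence wider relative uncertainty and possibly too few class (a) cases for a multivariable model.

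### Tolerance and withdrawal can supply two of the three criteria for dependence, with no rule for expected effects of repeated analgesic treatment, so prevalence may be inflated

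*Protocol article*

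**What the plan says.** The Telephone interview section sets the case definition. "Problematic use is abuse of or dependence on a substance according to the fourth edition of DSM (DSM-IV"), and each route has its own threshold. The dependence route is stated as "drug dependence by at least three of the seven DSM-IV criteria of substance dependence". The abuse route is lower: a single criterion out of four is enough. No criterion is qualified for a drug that was prescribed or given in hospital.

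Criteria are asked about during and outside pain episodes. The distinction enters under description and characterisation of problematic use, "by separating the pain-related criteria and non-pain-related criteria". Statistical methods follows the same order. The primary outcome is the unsplit frequency of EMONO problematic use in the overall study population. Pain-related and non-pain-related criteria are tabulated once the DSM-IV criteria are met.

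The Background gives the intended interpretation. It separates symptoms confined to pain, called pseudo-addiction, "from symptoms also occurring when there is no/mild pain, and more in favour of true addiction (rarer"). It also says of EMONO's active component: "Dependence on and tolerance to the effects of nitrous oxide have been demonstrated in animals and in humans". The Discussion adds that, with craving included, "finally, this set of criteria is consistent with the DSM 5 substance use disorders diagnostic criteria".

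**The concern.** The population has recurrent disease pain treated with EMONO and with WHO level II and III analgesics, at home and in hospital. After repeated exposure, tolerance and withdrawal can be ordinary pharmacological effects of treatment and need not indicate misuse. Under the stated rule each counts as a full criterion.

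Two results are at stake. The first is prevalence: a heavily treated patient may start two criteria closer to the threshold than a lightly treated one. Problematic use would then partly track treatment intensity, which also affects the planned analysis of its relationship with therapeutic data. The second is the separation of pseudo-addiction from true addiction. Withdrawal follows reduction or stopping of a drug, which may come when pain has eased, and the Background's general wording could place it on the addiction side. The Discussion expects this separation to guide management in different directions, and the Background's stated worry is that patients in pain are wrongly seen as addicted.

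**Working it through.** The article calculates no sample size and gives no expected prevalence, so there is no figure of its own to reproduce. The check is of the counting rule, followed by an illustration.

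**Inputs from the article.** Dependence: at least 3 of 7. Abuse: at least 1 of 4. Problematic use: either one.

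**Input from the named instrument.** Tolerance and withdrawal are two of the seven dependence criteria and none of the four abuse criteria. The article does not list the criteria and does not mention withdrawal.

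**Counting rule.**
- Tolerance and withdrawal alone: 2 < 3, so not dependent, and no abuse criterion is met. Not a case.
- Both present: 1 of the remaining 5 dependence criteria suffices.
- One present: 2 of the remaining 5 are needed.
- Neither present, or neither counted: 3 of the remaining 5 are needed.

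**Illustration (all rates assumed, all criteria independent).** Let each of the other five dependence criteria have rate p. At p = 0.10:
- at least 1 of 5: 1 − 0.9^5 = 41.0%
- at least 2 of 5: 8.1%
- at least 3 of 5: 0.9%

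For a treated group with tolerance 30% and withdrawal 20%, the shares are both 0.30 × 0.20 = 0.06, exactly one 0.30 × 0.80 + 0.20 × 0.70 = 0.38, and neither 0.70 × 0.80 = 0.56. Dependence is 0.06 × 41.0% + 0.38 × 8.1% + 0.56 × 0.9% = 6.0%. With tolerance 50% and withdrawal 30%, the shares are 0.15, 0.50 and 0.35, and dependence is 10.5%. Without the two criteria it is 0.9%.

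**From dependence to the endpoint.** Give the four abuse criteria the same rate: P(abuse) = 1 − (1 − p)^4 = 34.4% at p = 0.10. Problematic use = 1 − (1 − dependence)(1 − abuse):
- as written: 1 − (1 − 0.0603)(1 − 0.3439) = 38.3%, up to 1 − (1 − 0.1052)(1 − 0.3439) = 41.3%
- without the two criteria: 1 − (1 − 0.0086)(1 − 0.3439) = 35.0%

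The same steps at other values of p:

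| p | Dependence, as written | Dependence, without the two | Problematic use, as written | Problematic use, without the two |
|---|---|---|---|---|
| 0.05 | 2.3-4.6% | 0.1% | 20.4-22.3% | 18.6% |
| 0.10 | 6.0-10.5% | 0.9% | 38.3-41.3% | 35.0% |
| 0.20 | 17.3-25.2% | 5.8% | 66.1-69.4% | 61.4% |

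**EMONO.** The article supports tolerance to nitrous oxide but gives nothing on withdrawal from EMONO. With tolerance 30-50%, withdrawal 0 and p = 0.10, problematic use is 36.4-37.3% against 35.0%.

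**Does the split correct the count?** No. It is applied to patients who already meet the rule, so it cannot change who is a case.

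**The case against.** The unmodified DSM-IV threshold is a recognised standard, and using it is neither an error nor a contradiction. Problematic use is deliberately broad: pseudo-addiction is meant to fall inside it and be separated afterwards. Frequencies per criterion and per drug are planned, so readers will see how often each criterion contributes. The interview guide is not shown and may qualify these items. The Background sentence is an interpretation and not a scoring rule, and a symptom that appears only after pain ends fits neither of its two categories cleanly. Abuse needs one criterion of four, so the abuse route dominates the endpoint in the illustration.

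Much of this stands. It limits the point to a sensitivity analysis and makes the withdrawal reading a possibility. It does not remove the point. Per-criterion frequencies do not show how many patients would drop below three, because that depends on which criteria occur together in the same patient. The published rule contains no qualification.

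Three stronger readings are tempting and are not supported. A reader might infer that normal physical dependence by itself becomes problematic use; two criteria do not reach three. A reader might take the roughly sevenfold to twelvefold difference in dependence at p = 0.10 as the inflation of the endpoint; under the same assumptions the endpoint rises from 35% to about 38-41%. A reader might say the plan classifies withdrawal outside pain as true addiction; the article never mentions withdrawal, and this is only what its general wording allows.

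**Conclusion.** The point holds in limited form, as a cheap improvement and not as a flaw in the primary count. Expected effects of repeated treatment can supply two of the three dependence criteria, and one further criterion then suffices. The direction is upward: removing the two criteria can only lower the count or leave it unchanged. Dependence prevalence is the more exposed figure. In the illustration problematic use rises by about 3 to 6 percentage points at p = 0.10, and by about 1 to 2 points for EMONO with tolerance only.

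These sizes rest on assumed rates, on independence between criteria, which is doubtful within one syndrome, and on a repeatedly treated group. The planned denominator is the overall study population, so less exposed subjects would dilute the effect. The true size cannot be known from the document. The conclusion also relies on the content of the named instrument and on there being no qualifying rule in the interview guide.

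**What to change.** Keep the DSM-IV rule as the primary count. In Statistical methods, add for EMONO and for each other analgesic a sensitivity prevalence rescored without tolerance and withdrawal: at least 3 of the remaining five dependence criteria, or at least 1 abuse criterion. Apply it to all users of the drug. Restricting it to drugs taken as prescribed would need information the article does not show is recorded: the analgesic list form holds names and frequencies, and the clinical assessment holds treatment received.

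State also, where pseudo-addiction is separated from true addiction, that withdrawal alone is not counted as a non-pain-related criterion.

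The cost is small. The interview already collects a response to each criterion per drug, so this is rescoring plus one more column in the tables. The drawback is a second, lower prevalence to explain, and the stricter version may miss some true cases. The two figures should therefore be shown side by side.
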